### 3.10.2. Statistical methods

**Principles of statistical analysis:**

All statistical analyses were performed using IBM SPSS (version 26).

Demographic analysis will be performed in FAS population, the primary analysis (safety) will be performed in the SS population, and the secondary analysis (immunogenicity) will be performed both in the FAS and PPS population.

The Kolmogorov-Smirnov test was used to evaluate the distribution types. Non-normally distributed and ordered data are represented by the median (range). Measurement of pseudovirus 50% neutralization titers (pVNT_50_s) are represented by geometric means. Pearson’s chi-square test, continuity correction, and Fisher’s exact test were used to check the proportion of the count data.

The Mann-Whitney U test and paired t-test were used to compare differences between groups, the Wilcoxon rank-sum test was used to compare intragroup differences, and the nest t-test was used to compare unmatched groups. We displayed the median values of each group in the figures using GraphPad Prism 8 and estimated the differences based on the 95% confidence interval (CI).

Baseline characteristics were screened using univariate logistic regression, and the significantly different factors (*P*_value<0.1) were further analyzed using multivariate logistic regression. The analysis results are presented using an OR combined with a 95% CI (lower–upper) in the table.

In correlation analysis, the Pearson correlation test was used to process normally distributed datasets, while the Spearman rank correlation test was used to process non-normally distributed datasets. An absolute R value>0.5 indicated a strong correlation, whereas an absolute R value≤0.5 indicated a weak correlation.

The hypothesis test was bilateral, and a *P*_value<0.05 was considered statistically significant.

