## 3.6. Sample size

The target sample size is 300 participants. The allocation ratio will be 2:1, with 200 participants in the elderly experimental group (aged 60–80) and 100 participants in the younger control group (aged 18–59).

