**Demographic analysis:**

The analysis of baseline demographic information will be based on the FAS population.

This includes a statistical description and comparison of baseline demographic information (including age, gender, BMI, laboratory test indices, and comorbidities) to measure comparability between the two groups. Summarized statistical data will be used based on the properties of the variables (continuous or categorical).

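### Baseline factors are selected at univariate P<0.1 and the survivors' ORs get ordinary 95% CIs, which do not have 95% coverage after that selection

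*Protocol*

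**What the plan says.** The general principles in section 3.10.2 set out a sequence. First, "Baseline characteristics were screened using univariate logistic regression". Then "the significantly different factors (*P*_value<0.1) were further analyzed using multivariate logistic regression". Finally, "The analysis results are presented using an OR combined with a 95% CI (lower–upper) in the table". The same paragraphs set a two-sided 0.05 level for all tests. No correction for the selection step, no multiplicity rule and no exploratory label is attached.

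The dependent variable of the logistic models is not named. The candidate factors are not listed next to the method; the nearest list is under Demographic analysis, which compares "age, gender, BMI, laboratory test indices, and comorbidities" between the two age groups. Section 3.6 gives the size: "The target sample size is 300 participants", 200 elderly and 100 younger. Groups are formed by age, without randomisation (section 3.8.1 and the trial summary).

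The primary, secondary, breakthrough-infection and pseudovirus sections specify chi-square or Fisher tests, Mann-Whitney tests, a nested t-test and correlations. None of them calls on this logistic model.

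**The concern.** A 95% CI has its stated coverage when the model is fixed before the outcome is seen. Here the same data decide which factors are shown and then supply the intervals for those shown. A factor with no effect enters the table only if chance has moved its univariate estimate far enough from OR=1 to reach P<0.1, so the displayed estimate tends to be too far from the null and its interval too often misses the truth. Weak real effects are overstated for the same reason.

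A second problem is that a univariate screen judges each factor without the others. A factor whose effect is masked by a correlated one can fail the screen and never reach the adjusted model. Age group is exposed to this: it is the trial's central contrast, it is not randomised, and older participants can be expected to differ in laboratory values and comorbidities.

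At stake is whether a reader can take the OR table at face value.

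**Working it through.** **Nothing to reproduce.** The protocol states no power, error rate or coverage for this step, so the check asks how the stated procedure behaves.

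**Inputs from the protocol.** n=300 (section 3.6); screening threshold P<0.1; reported intervals 95%; significance level 0.05 two-sided (section 3.10.2).

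**Assumptions.** Number of candidates k = 5 to 20. The Demographic analysis list includes laboratory indices, and the schedule footnote shows that these span liver and kidney function, glucose and lipids, so 10 to 20 is plausible. Outcome rate 25% (20% and 50% also tried). Pairwise correlation between factors 0, 0.2 or 0.3.

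**Step 1, one null factor by hand.** If the factor is independent of the others, its adjusted and univariate z-statistics nearly coincide. It is retained with probability 0.10, and its 95% CI misses OR=1 with probability 0.05. Coverage given retention is therefore

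(0.10 − 0.05) / 0.10 = 0.50.

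**Step 2, how often the table contains such a factor.** For k independent null factors, the chance that at least one passes the screen is 1 − 0.9^k:
- k=5: 41%
- k=10: 65%
- k=20: 88%

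**Step 3, simulated coverage of retained null factors.** Each run makes a univariate logistic screen at P<0.1, fits a multivariable model on the survivors, and compares it with one unscreened model on the same data.

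| Setting | Screened | Unscreened |
|---|---|---|
| No true effects, 25% outcome rate, k=5-20, correlation 0 to 0.2 | about 50-72% | 94-95% |
| Two true effects, k=10, 20% outcome rate, correlation 0 | 51-53% | 95% |
| Two true effects, k=10, 20% outcome rate, correlation 0.3 | 90-98% | 95% |

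The lower end of the first row agrees with step 1. In the last row null factors are often retained because they are correlated with real ones, and the adjusted fit then brings them back towards the null, so coverage largely recovers. For weak true factors (OR 1.22, n=300, uncorrelated) the retained OR averages 1.42, with coverage 93%.

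**Step 4, interval width.** Standard errors of survivors are only about 1-11% smaller than in the unscreened model. That is too little to explain coverage near 50%; the cause is the displacement of the estimates by selection.

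**Step 5, spurious significant factors.** With no true effects and independent factors, the chance that at least one factor reaches P<0.05 is 1 − 0.95^k, which is 23%, 40% and 64% for k = 5, 10 and 20. The simulated screened procedure gives 21-22%, 37-40% and 61-63%; the unscreened model gives 22-23%, 40-42% and 66-70%. With 15 candidates at correlation 0.2 the figures are 34% screened against 52% unscreened. The screen does not raise this rate.

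**Step 6, dropping age group.** As an illustration, take 200 elderly and 100 younger participants, a comorbidity burden 0.8 SD higher in the elderly, a log-OR of 0.6 per SD of burden and −0.5 for age group. The unadjusted log-OR for age group is roughly 0.6 × 0.8 − 0.5 = −0.02, so the univariate test has almost nothing to detect and age group should fail P<0.1 about 90% of the time. Simulation gives 91%, although the adjusted effect is real. These effect sizes are chosen to show masking, not to estimate how likely it is in this trial.

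**The case against.** A reader might infer that the screen manufactures false risk factors. Step 5 does not support that: an unscreened model with the same long list yields as many or more factors at P<0.05. Those findings come from testing many factors at 0.05 without a multiplicity rule or an exploratory label.

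A reader might also describe the intervals as simply too narrow. Step 4 shows that width is a minor part; the estimates are in the wrong place.

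Nor should the effect be read as touching the trial's conclusions. The protocol names no outcome for these models and does not speak of risk factors. The phrase about significantly different factors could even mean characteristics that differ between the age groups. No stated endpoint comparison is adjusted, so a dropped covariate cannot bias one.

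The size is also conditional. The low coverage belongs to null factors that are retained, and in the correlated setting with true effects it is close to nominal.

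Finally, outcome, covariates and exploratory status are often left to a statistical analysis plan. That does not remove the point, because the protocol does not leave the method open: it states the screen, the threshold and the form of report. A later plan would have to depart from it. Section 3.9 also lists discussion of the statistical plan after database lock, which is late for choosing covariates.

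What stands of the objection is the limit on reach and size, and both are carried into the conclusion.

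**Conclusion.** The point holds in a limited form. The protocol fixes a selection step on the same data and then reports intervals that ignore it. With no true effects, and under the assumed 5 to 20 candidates, n=300 and a 25% outcome rate, retained factors' 95% CIs cover the truth in about 50-72% of cases instead of 94-95%. The loss depends on the number, correlation and strength of the factors, none of which the protocol gives, and it can nearly vanish. The screen can also remove a factor that matters after adjustment, age group included. The consequence is confined to a supporting table whose outcome is unnamed. The step is worth correcting because the stated method is unsound and the change is cheap; it does not threaten the primary or secondary analysis.

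**What to change.** In section 3.10.2:

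1. Delete the univariate P<0.1 step.
2. Name the binary outcome or outcomes to be modelled, for example any adverse event within one month of a dose, or breakthrough infection.
3. Fit one logistic model per outcome with a short covariate set fixed in advance from data already collected, for example age group, sex, BMI, hospital and any comorbidity. If events are few, shorten the list in a stated order or use a penalised fit.
4. Report every OR with its 95% CI, whatever its P value.
5. Label the table exploratory and make no P<0.05 claims about individual factors. This is needed as well as step 3: five fixed null covariates still give at least one P<0.05 in about 21-24% of analyses.

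The cost is wording only, with no new data, visits or participants. The downside is that non-significant factors stay in the table.

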**Pseudovirus neutralization test analysis**

Based on the FAS population, an equal number of participants were randomly selected from both groups, ensuring no significant intergroup differences in gender and age, and no missing values at baseline and follow-up points at the 2^nd^, 7^th^, 8^th^, 13^th^, and 16^th^ months. The analysis of antibody-positive rates and titers (pVNT_50_s) is in the same way as the **Secondary analysis** mentioned above.

(1) Correlation between pVNT_50_s and symptoms

The infection status within the two groups will be statistically described, and the corresponding pVNT_50_s will be treated as continuous variables. An intergroup comparison will be performed using the nested t-test, and the corresponding geometric means and 95% CIs will be provided.

(2) Correlations between wild-type SARS-CoV-2–specific pVNT_50_s and variant-specific pVNT_50_s

The pVNT_50_s measured at each follow-up point will be statistically described as continuous variables. The Kolmogorov–Smirnov test will be utilized to evaluate data normality, followed by the Pearson correlation test or the Spearman rank correlation test for correlation analysis.

(3) Correlations between different variant-specific pVNT_50_s

The pVNT_50_s measured at each follow-up point will be statistically described as continuous variables. The Kolmogorov–Smirnov test will be employed to evaluate data normality, followed by the Pearson correlation test or the Spearman rank correlation test for correlation analysis.

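### A Kolmogorov-Smirnov pre-test picks Pearson or Spearman for each pVNT50 dataset and both are read against one 0.5 cut-off; one coefficient on one scale should be fixed instead (minor, exploratory analysis)

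*Protocol*

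**What the plan says.** Protocol section 3.10.2, under the principles of statistical analysis, sets the general rule. The distribution check is named: "The Kolmogorov-Smirnov test was used to evaluate the distribution types". The coefficient follows from its result: "the Pearson correlation test was used to process normally distributed datasets, while the Spearman rank correlation test was used to process non-normally distributed datasets". One scale of interpretation then serves both coefficients: "An absolute R value>0.5 indicated a strong correlation, whereas an absolute R value≤0.5 indicated a weak correlation".

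The pseudovirus neutralization part of the same section applies this to two sets of correlations, wild-type against variant titres and variant against variant titres: "The Kolmogorov–Smirnov test will be utilized to evaluate data normality, followed by the Pearson correlation test or the Spearman rank correlation test". The scale is described only as follows: "The pVNT_50_s measured at each follow-up point will be statistically described as continuous variables". Elsewhere in section 3.10.2 the same titres are summarised on a multiplicative scale: "Measurement of pseudovirus 50% neutralization titers (pVNT_50_s) are represented by geometric means".

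The subset is described by how it is drawn, "an equal number of participants were randomly selected from both groups", and by complete data at baseline and five follow-up months. No number is given. Section 3.6 plans 100 younger participants, so the subset cannot exceed about 100 per group.

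**The concern.** Reporting titres as geometric means treats them as roughly log-normal. On such data Pearson on the untransformed values and Spearman are different parameters, and Pearson is pulled by a few high titres. A rule that switches between them according to a pre-test can give one variant pair a Pearson at one visit and a Spearman at the next, with both read against the same 0.5.

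An apparent change in cross-variant correlation between visits or variants, or a move from strong to weak, could then come from the switch rather than from the immune response. The choice of pre-test adds to this. KS critical values derived for a fully specified normal are very conservative when mean and SD are estimated from the sample, so skewed titres can pass as normal when n is small.

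**Working it through.** The protocol gives no power or error figure for this analysis, so there is nothing of its own to reproduce.

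**Inputs from the protocol.** KS gate, Pearson or Spearman by its result, cut-off 0.5 for both, significance level 0.05, at most about 100 per group.

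**Assumed inputs, shown as ranges.** Log-normal titres with ln SD (s) 0.8–1.0; log-scale correlation (ρ) 0.6, 0.8 or 0.9; n from 20 to 100. Pearson is taken as chosen only when both variables of a pair pass; the protocol does not say what happens when one passes and the other fails.

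**Step 1: do the coefficients differ?** For bivariate log-normal titres:
- Pearson, untransformed = (exp(ρs²) − 1) / (exp(s²) − 1)
- Spearman = (6/π) × arcsin(ρ/2)

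With ρ = 0.6 and s = 1.0: Pearson = (1.822 − 1)/(2.718 − 1) = 0.48; Spearman = 1.910 × arcsin(0.3) = 0.58. They lie on opposite sides of 0.5.

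With ρ = 0.6 and s = 0.8: Pearson = (1.468 − 1)/(1.896 − 1) = 0.52; Spearman is again 0.58. Both exceed 0.5, so at this spread a label changes only through sampling variation.

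**Step 2: how often does a single log-normal variable pass as normal?** By simulation, with the sample mean and SD plugged in (s = 0.8 / 1.0):

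| n | Uncorrected KS | Lilliefors |
|---|---|---|
| 20 | 90% / 79% | 35% / 23% |
| 30 | 76% / 57% | 17% / 7% |
| 50 | 47% / 20% | 3% / 0.4% |
| 100 | 5% / 0.2% | 0% / 0% |

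Under true normality the uncorrected test rejects in 0–0.02% of samples instead of 5%.

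**Step 3: how often is Pearson chosen for a pair?** Uncorrected KS, ρ = 0.6: about 66–83% at n=20, 36–61% at n=30, 5–24% at n=50 and under 1% at n=100. With Lilliefors at n=20–30: about 1–14%.

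**Step 4: how often does the gate change the label?** The relevant count is the share of datasets in which Pearson is chosen and its label differs from Spearman's.

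| Setting | Label changed |
|---|---|
| Uncorrected, n=20–30, ρ = 0.6 | 12–23% |
| Uncorrected, n=20–30, ρ = 0.8 | 2–7% |
| Uncorrected, n=20–30, ρ = 0.9 | 0.3% or less |
| Uncorrected, n=60, ρ = 0.6 | 0.6–4% |
| Uncorrected, n=100, ρ = 0.6 | under 1% |
| Lilliefors, n=20–30, ρ = 0.6 | about 0.1–3% |

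**The case against.** The strongest reply is that a serious effect needs three conditions that the protocol does not state. A reader might infer all three.

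- **Uncorrected KS.** The protocol names the test and the software but no variant or set of critical values. The lack of a stated correction does not show that none is used, and this detail may be left to an analysis plan.
- **A small subset.** No size is given, and up to about 100 per group is possible. The correlations are not said to be run by group, so 20–30 per group could mean 40–60 pooled.
- **Untransformed titres.** The word measured in the pseudovirus section refers to the visit, not to the scale. The geometric means suggest that the log scale may be intended. On that scale normality is plausible and the two coefficients nearly coincide (0.60 against 0.58), so the gate would do little harm.

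A reader might also compare Pearson with Spearman on every simulated dataset, find opposite labels in roughly a third at ρ = 0.6, and call that the effect of the rule. It is not, because it includes datasets that the gate already sends to Spearman. It is also taken at a correlation close to the cut-off. Even log-scale Pearson and Spearman give different labels in 12–14% of datasets at n=20–30 and ρ = 0.6, so part of any disagreement is noise around a threshold.

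These points stand and they limit the size of the problem. They do not remove the rule. The protocol itself fixes a data-driven choice between two coefficients and one cut-off for both, and it leaves open the three facts that would show the choice to be harmless.

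**Conclusion.** The point holds as a minor, conditional one. The rule switches, dataset by dataset, between coefficients that differ on skewed titres, and reads them as if they were the same.

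If uncorrected KS is applied to untransformed log-normal titres in about 20–30 participants, the gate alters the strong or weak label in roughly one dataset in eight to one in four when the log-scale correlation is 0.6. The effect is small at correlation 0.8, at most about 3% with a Lilliefors correction, and under 1% at n=100. The subset size, titre spread, correlation and KS version behind these figures are assumptions.

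The documents do not support saying that skewed titres will be passed as normal, or that a third of the labels will be wrong. The correlations are exploratory and touch neither the primary safety endpoint nor the secondary antibody-titre endpoint.

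**What to change.** In section 3.10.2, in both the principles of statistical analysis and the pseudovirus neutralization analysis, remove the KS gate for correlations. Name one coefficient on one scale for every variant pair and visit: Pearson on log10 pVNT50, which agrees with the geometric means, or Spearman throughout if many values lie at the detection limit. Report each coefficient with a 95% confidence interval, so that the reading does not rest on the 0.5 label alone.

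The cost is a change of wording. The data are the same, the analysis is simpler, and the case in which only one variable of a pair passes the test no longer needs a rule.

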**Demographic analysis:**

The analysis of baseline demographic information will be based on the FAS population.

This includes a statistical description and comparison of baseline demographic information (including age, gender, BMI, laboratory test indices, and comorbidities) to measure comparability between the two groups. Summarized statistical data will be used based on the properties of the variables (continuous or categorical).

**Primary analysis:**

The main endpoint of this study is the safety after vaccination, which involves the evaluation of AEs, SAEs, and laboratory test indices, and performed on the SS.

The AEs/SAEs occurring in the two groups within one month after each dose of vaccination will be statistically described as a categorical variable, and Pearson’s chi-square test or Fisher’s exact test will be used for intergroup comparisons. The AEs/SAEs of the different categories will be summarized in percentages. The laboratory test indices at each follow-up point will be statistically described as continuous variables, and the Mann–Whitney U test will be used for intergroup comparisons. The median values of the laboratory test indices for the two groups will be calculated at each follow-up point, as well as the corresponding intergroup differences and 95% CIs.

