| Key eligibility criteria | **Inclusion criteria**   1. Signed informed consent; 2. In females, the urine pregnancy test was negative; 3. At least 6 months of follow-up was completed; 4. HBsAg, anti-HCV, HIV, treponema pallidum hemagglutination assay (TPHA) screening was negative; 5. Armpit temperature was ≤37.0℃; 6. The young group was aged 18–59 years, and the elderly group between 60–80 years.   **Exclusion criteria**   1. In females, the urine pregnancy test positive; 2. Pregnant or lactating women; 3. Known allergies to certain components of these two vaccines; 4. Patients with serious chronic diseases or advanced diseases such as high blood pressure, diabetes, asthma, thyroid disease, *etc*. which cannot be controlled by drugs; 5. Those suffering from thrombocytopenia, hemorrhagic disease or thrombotic disease; 6. Those with congenital or acquired angioedema/neuroedema; 7. Those with a history or family history of convulsions, epilepsy, encephalopathy, other progressive neurological diseases, and psychiatric disorders; 8. Lymphadenopathy； 9. Lymphoma, leukemia and other systemic malignancies; 10. Autoimmune disease; 11. Chronic diseases with cute exacerbation or acute infectious diseases and fever. |
| Study design | Study type: Prospective real-world interventional trial  Allocation: Open, non-randomized  Intervention model: Parallel group  Primary purpose: Prevention |
| Date of enrolment | July 1, 2021 |
| Target sample size | 300 (200 in the elderly group, 100 in the young group) |
| Recruitment status | Recruited |
| Primary outcomes | **Primary endpoint measures**   - Safety profiles within one month after each vaccination dose, including:   1. The incidence of adverse events;   2. Liver function;   3. Kidney function;   4. Blood glucose;   5. Blood lipids. - The definition and grade of adverse events (AEs) were evaluated according to the Common Terminology Criteria for Adverse Events (CTCAE), version 5.0:  1. Grade 1 (mild) - asymptomatic or mild symptoms, clinical or diagnostic observations only, intervention not indicated; 2. Grade 2 (moderate) - minimal, local, or non-invasive intervention indicated, limiting age-appropriate instrumental activities of daily living (ADL); 3. Grade 3 (severe or medically significant but not immediately life-threatening) - indication for hospitalization or prolongation of hospitalization, disabling and limiting self-care ADL. |

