# 3. METHODS

## 3.1. Study setting

This trial will be conducted in two hospitals: the Hunyuan County People's Hospital, Datong 037499, Shanxi Province, China; and the Fifth Medical Center of Chinese PLA General Hospital, Beijing 100039, China.

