## 3.8. Allocation and vaccine management

### 3.8.1. Allocation

The participants will be assigned to either the experimental or control group in a 2:1 ratio based on age.

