**Secondary analysis:**

The secondary endpoint of this study is the immunogenicity after vaccination, which is performed on the FAS and PPS.

The antibody-positive rates at each follow-up point in the two groups will be statistically described as categorical variables, and Pearson’s chi-square test or Fisher’s exact test will be used for intergroup comparisons. The antibody titers at each follow-up point in the two groups will be statistically described as continuous variables, and the Mann–Whitney U test will be employed for intergroup comparison. For the absolute titers of neutralizing antibodies and anti-RBD antibodies, the median values of antibody titers will be calculated for the two groups at each follow-up point, as well as the corresponding intergroup differences and 95% CIs. For the relative titer values of variant-specific neutralizing antibodies, the geometric mean of the antibody titers for the two groups will be determined at each follow-up point, as well as the corresponding intergroup differences and 95% CIs.

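### The elderly–young tests take no account of hospital and no age ratio is fixed within hospital, so a site difference can bias the contrast if the age mix differs by site

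*Protocol*

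**What the plan says.** Section 3.1 states: "This trial will be conducted in two hospitals", one a county hospital in Shanxi and the other in Beijing. The Trial Summary gives the design as "Allocation: Open, non-randomized".

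Section 3.8.1 describes how the groups are formed: "The participants will be assigned to either the experimental or control group in a 2:1 ratio based on age". Section 3.6 gives the totals, "with 200 participants in the elderly experimental group (aged 60–80) and 100 participants in the younger control group (aged 18–59" years. Neither section, nor 3.7 on recruitment, sets a ratio or quota per hospital.

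Section 3.10.2 names the between-group tests:
- AEs/SAEs (primary analysis): "Pearson’s chi-square test or Fisher’s exact test will be used for intergroup comparisons".
- Laboratory indices (primary analysis): "the Mann–Whitney U test will be used for intergroup comparisons".
- Antibody titres (secondary analysis): "the Mann–Whitney U test will be employed for intergroup comparison". Antibody-positive rates get chi-square or Fisher tests.

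None of these is stratified or adjusted. The baseline comparison in the same section lists its variables as "including age, gender, BMI, laboratory test indices, and comorbidities) to measure comparability between the two groups". Hospital is not among them.

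**The concern.** Age cannot be randomised, so the only between-group comparison in the study has no design protection against other differences between the groups. Recruiting hospital is one such difference. Unlike BMI or comorbidity, it is not plausibly a consequence of ageing, so adjusting for it does not remove part of the effect of interest.

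Suppose one hospital supplies a larger share of the elderly than of the young. Suppose too that the hospitals differ in how completely AEs are recorded, in background laboratory values or in titres. A crude test then attributes part of the site difference to age. At stake are the comparative safety statement, which is the primary endpoint, and the comparative immunogenicity statement. Both conditions are needed: with only one of them, there is no bias.

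**Working it through.** **Inputs from the protocol.** n = 200 elderly and 100 young (3.6); two-sided test at 0.05 (3.10.2); two hospitals (3.1). The sample size is internally consistent: 200 + 100 = 300 and 200:100 = 2:1. No power, effect size or event rate is given, so there is no sample-size calculation to reproduce.

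**Assumed inputs.** The protocol gives no AE rate by site, titre shift by site or age-by-site split. All three are varied below. The true age effect is set to zero throughout.

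**Bias formula.** Let hospital A have AE rate p_A and hospital B have p_B. Let f_E and f_Y be the shares of elderly and young enrolled at A. The crude difference expected with no age effect is

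(p_A − p_B) × (f_E − f_Y).

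**Worked case.** p_A = 20%, p_B = 10%, f_E = 70%, f_Y = 30%.
- Elderly: 0.7 × 20 + 0.3 × 10 = 17%.
- Young: 0.3 × 20 + 0.7 × 10 = 13%.
- Spurious difference: 17 − 13 = 4 points = 10 points × 0.4.
- Pooled rate: (200 × 17 + 100 × 13)/300 = 15.67%. Null standard error: √[0.1567 × 0.8433 × (1/200 + 1/100)] = 0.0445, so the critical difference is 1.96 × 0.0445 = 0.087.
- Actual standard error: √[0.17 × 0.83/200 + 0.13 × 0.87/100] = 0.0429.
- Rejection probability: P(Z > (0.087 − 0.04)/0.0429) + P(Z < (−0.087 − 0.04)/0.0429) ≈ 13.7%. Simulation gives 13.4%.

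**AE false-positive rates, simulated.** A range shows the two directions of imbalance: the lower value has most elderly at the higher-capture hospital, the higher value has them at the lower-capture one.

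| Share at one site, elderly v young | Bias, 20% v 10% | Crude test | Bias, 30% v 10% | Crude test |
|---|---|---|---|---|
| Equal | 0 | about 5% | 0 | 4–5% |
| 60 v 40 | 2 points | 7–8% | 4 points | 11–13% |
| 70 v 30 | 4 points | 13–16% | 8 points | 35–39% |
| 80 v 20 | 6 points | 25–30% | 12 points | 68–72% |

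A Cochran–Mantel–Haenszel (CMH) test stratified by hospital rejects in 4.8–5.1% of trials in every row.

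**Titres.** On the log scale the bias is again the site shift times the mix gap. A 0.2 log10 shift with a 40-point gap gives a spurious ratio of 10^(0.2 × 0.4) = 1.20. In SD units, the crude Mann–Whitney test rejects as follows:

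| Share at one site, elderly v young | Site shift 0.3 SD | Site shift 0.5 SD |
|---|---|---|
| 50 v 50 | 5% | 4% |
| 60 v 40 | 7% | 11% |
| 70 v 30 | 15% | 34% |
| 80 v 20 | 29% | 66% |

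**The case against.** **The sizes are assumed.** This stands. The protocol gives no split by site, and a mild imbalance costs little: 7–8% at 60/40 v 40/60 with 20% v 10% capture. Section 3.12 also requires a unified protocol and joint training at both hospitals, which makes a twofold or threefold difference in AE capture harder to presume. Those are conduct rules, however. They cannot equalise the two catchment populations and they do not adjust the analysis.

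**Site adjustment belongs in the SAP.** An unseen plan may add it, and section 3.9 mentions a statistical plan to be discussed. But the protocol does not leave the choice open here. It names the unstratified tests, and an SAP that follows it would inherit them.

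**There is a multivariable model.** Section 3.10.2 includes a logistic regression on baseline factors screened at P<0.1. It names neither an outcome nor hospital, it is not the stated primary analysis, and it would not adjust continuous titres or laboratory values.

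**The contrast is not confirmatory.** The stated objective (2.2) concerns the elderly, section 2.3 calls the study single-arm, and no contrast is powered. This lowers the severity. The protocol nevertheless prescribes these tests with a 0.05 threshold, and their results will be read as age effects.

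**A stronger reading to avoid.** A reader might infer that any site difference will be read as an age effect. The documents do not support that: if both hospitals enrol the age groups in the same ratio, the bias is zero.

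**Conclusion.** The point holds in conditional form. The protocol fixes crude tests for its only between-group contrast, in a non-randomised two-hospital study with no control of age mix within hospital. Whether bias results depends on two facts that the protocol does not state: the age mix at each hospital and the difference in outcomes or AE capture between them.

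Under the assumed 20% v 10% capture, the crude false-positive rate runs from the nominal 5% at equal mix to 25–30% at 80/20 v 20/80. Larger assumed site differences take it further. The stratified test holds about 5% whether or not the mix is balanced, so little is lost by using it. This is a worthwhile, inexpensive improvement to a stated analysis. It does not show that the results are wrong.

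**What to change.** 1. Tabulate age group by hospital first, and add hospital to the baseline comparison.
2. For the AE contrast, use a CMH test stratified by hospital, with a common risk difference and its interval. Where events are sparse, as SAEs may be, use an exact stratified test, so that the protection of the planned Fisher option is kept. Treat antibody-positive rates in the same way.
3. For titres and laboratory values, use a van Elteren test stratified by hospital, or a log-scale model with a hospital term. Sex may be added. Leave BMI and comorbidity out of the main adjusted contrast, since they may lie on the path from age to outcome.
4. Keep the crude tests as descriptive.

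The cost is a change of wording and modest analysis work; recruiting hospital should be known for every participant, and nothing in trial conduct changes. The downside is wider intervals when the mix is very unequal. If each hospital enrols only one age group, the stratified contrast cannot be estimated, and the report must say that age and site are inseparable.
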